### Serious adverse events and adverse events

The assessment of serious adverse events and adverse events that occurred during the intervention will be assessed by a self-reported questionnaire, including the symptom and/or adverse event, with duration and intensity details. Serious adverse events will include any significant disability, hospitalisation, life-threatening, and death and will be reported immediately to the researchers and ethics committee.

### Data collection and management

Patient’s characteristics at baseline assessment will be collected immediately before randomisation. All the data collected, and outcomes will be obtained using printed questionnaires.

#### Baseline assessment

A self-administered questionnaire will be filled out by the participants regarding sociodemographic characteristics and personal data (age, sex, marital status, profession, education level, address, telephone, e-mail) and anthropometric data (weight, height, and body mass). Subsequently, body mass index (BMI) will be calculated by weight in kilogrammes divided by height in metres squared (kg/m^2^). BMI categories will be divided into underweight (BMI < 18.5), normal weight (BMI 18.5 to 24.9), overweight (BMI 25.0 to 29.9), and obese (BMI ≥30.0). The schedule will be performed as presented in Fig. 1.

**Fig. 1 Fig1:**
[figure not shown]
Schedule of enrolment, interventions, and assessments. *Sociodemographic, clinical, personal, and anthropometric characteristics. **Primary outcome: pressure pain threshold and postural instability. Secondary outcome: pain intensity and patient’s expectation. ***Adverse events

#### Data management

The original data will be scanned as image files by a research assistant and shared with a second research assistant. All data will be stored in a password-protected computer and data integrity will be checked regularly for omissions and errors by double entered with automated checks in Microsoft Excel spreadsheet (Microsoft Corporation) performed remotely by an independent examiner. Discrepancies will be resolved by checking the original data.

#### Confidentiality

Participants will be identified by an individual trial number to ensure confidentiality, and confidentiality regarding the data collected in all stages will be guaranteed.

### Statistical analysis

#### Sample size calculation

The sample size calculation was performed a priori in the software G * Power version 3.1 (Heinrich-Heine-Universität, Düsseldorf, Germany) to determine a sufficient sample size. According to a model used previously [18] in individuals with LBP to detect a minimum difference of 15% (effect size of 0.64) in the low-pressure pain threshold, the statistical power of 80%, and an alpha of 0.05 in a two-way analysis of variance (ANOVA) repeated measures, the estimated sample size was 40 patients per group. A total of 80 participants will be included in the present study.

#### Data analysis

The results will be tabulated in Microsoft Excel software and analysed by an independent researcher. The results of the descriptive analysis will be presented in mean and standard deviation (SD) for continuous variables, and absolute values and proportions (%) for categorical variables. The analysis of the data distribution on primary outcomes will be performed using the Shapiro-Wilk test. The comparison between the groups regarding the effect of interventions on pressure pain threshold, postural stability, and pain intensity will be performed by two-way ANOVA. The Bonferroni post hoc test will be used when a significant *F* value is found. For each ANOVA, the metric of interest will be bidirectional interaction (intervention group x evaluation time). All statistical tests will be two-tailed with the pre-established significance level at *p* < 0.05. All data will be analysed using the JASP version 0.14.1 software, and graphics analysis will be performed using GraphPad Prism software (GraphPad Software, San Diego, CA, USA) version 8.00 for MacBook.

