#### Primary outcome variables

##### Evaluation of the pain threshold

The evaluation of the pressure pain threshold will be performed by a trained evaluator using a digital pressure algometer with a 1-cm^2^ rubber probe. The device will be properly calibrated. The evaluation points will be measured bilaterally three times in the following places: the middle portion of the calf in the medial gastrocnemius muscle, anterior tibial muscle laterally at the level of the anterior tibial tuberosity, 2 cm laterally to the L5 spinous process, 2 cm laterally to the spinous process of L1, the medium portion of the deltoid muscle, and 2 cm distal to the lateral epicondyle. The probe will be placed perpendicular to the skin, and the pressure increased at a rate of 500 g/s while the examiner visually monitors the force in real time by reading the digital display. The participant will be instructed to say “stop” as soon as the pressure sensation becomes painful, the applicator will remove the algometer, and the threshold will be recorded electronically. For data analysis, the average of the three values obtained in each evaluation measure by pressure algometer in pre- and post-intervention will be used [34]. The minimal important clinical difference in the assessment of the pressure pain threshold considered will be at least 15% between pre- and post-intervention. The use of an algometer to assess the pressure pain threshold is considered to have excellent reproducibility and validity [35]. A study described inter-rater reliability for pressure pain threshold, and highly reliable measures can be found when pressure pain threshold is calculated as the mean of 3 measures [35].

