##### Evaluation of postural stability

The evaluation of postural stability will be performed in a baropodometry exam by displacing the CoP through the platform *FootWork*, with an active surface of 400 × 400 mm dimensions of 645×520×25 mm, and a USB-powered connection connected to a notebook. The evaluation will be carried out in a specific task with eyes open. Participants must remain standing on the platform keeping their eyes fixed on a mark 2 m away. The participant will be instructed to remain static, in an anatomical position with feet spaced at hip-width with elbows extended along the trunk, holding in each hand a bag that weighs 2 kg. During the examination, participants will remain barefoot on the baropodometer. The participant will then be instructed to perform as many as possible squats in 40 s. The stability variable investigated using the baropodometer will be the area of the CoP ellipse (A-CoP in millimetres squared). Improved postural stability is assessed by decreasing the oscillation of the CoP through baropodometry from the observation of a variation of at least 15% in the pre- and post-intervention measurements. A previous study carried out by our group showed that the barodometer is a valid instrument to measure postural stability through CoP (sway area) displacement in patients with nonspecific cLBP [36].

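### CoP ellipse area is tested as an unadjusted difference in mm² change although improvement is defined as a 15% relative change; prespecify baseline adjustment and the analysis scale

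*Protocol article*

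**What the plan says.** In the protocol article, Evaluation of postural stability names the stability variable as "the area of the CoP ellipse (A-CoP in millimetres squared". No other scale is named. The same section defines improvement as reduced oscillation, judged by a "variation of at least 15% in the pre- and post-intervention measurements". Evaluation of the pain threshold uses the same relative form for the other primary outcome: the minimal important difference "will be at least 15% between pre- and post-intervention".

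Data analysis states that the comparison of arms on "pressure pain threshold, postural stability, and pain intensity will be performed by two-way ANOVA", and that for each ANOVA "the metric of interest will be bidirectional interaction (intervention group x evaluation time". It also says "The analysis of the data distribution on primary outcomes will be performed using the Shapiro-Wilk test". It names no transformation, no adjustment for baseline, and nothing that follows from the Shapiro-Wilk result.

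Sample size calculation gives 40 per group, based on pressure pain threshold. It gives no figure for CoP area.

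**The concern.** With two assessments per participant, the group x time interaction is the between-arm difference in mean change, here in mm². Two things follow.

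First, the change score gives the baseline a fixed coefficient of 1 instead of estimating it. That wastes information whenever the pre-post correlation is below 1.

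Second, the tested quantity and the improvement criterion are on different scales. As an illustration, a fall from 1000 to 850 mm² and a fall from 100 to 85 mm² both just meet the 15% criterion. The first contributes 150 mm² to the mean change and the second 15 mm², ten times less. If areas are right-skewed, a few large ellipses can dominate the comparison.

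At stake are power and interpretability for a primary outcome that the sample size calculation did not address. A normality test with no stated consequence also leaves room for the analysis scale to be chosen after the data are seen.

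**Working it through.** **1. The plan's own figure.** Sample size calculation gives effect size 0.64, 80% power and alpha 0.05. Read as a two-group standardised difference, n per group = 2(1.96 + 0.842)²/0.64² = 38.3, so 39 by normal approximation. The noncentral t distribution gives power 0.797 at 39 and 0.807 at 40. So 40 per group reproduces on that reading. It concerns pressure pain threshold and says nothing about CoP area.

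**2. What baseline adjustment buys.** For a measure with equal SD σ at both times and correlation r:
- variance of the change score: 2σ²(1 − r)
- residual variance in ANCOVA: σ²(1 − r²)
- ratio of ANCOVA to change score: (1 + r)/2

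At r = 0.7 the ratio is 0.85, a 15% lower variance. The same formula applies to pressure pain threshold, on whatever scale it is analysed.

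**3. Power for CoP area.** From the documents: 40 per arm, two-sided alpha 0.05, and the 15% as a true reduction in one arm (ratio 0.85). Assumed, because the documents give no SD, skewness or correlation for CoP area: lognormal values, log-SD 0.3 to 0.8, r = 0.7. Simulated power:

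| Log-SD | mm², interaction | mm², ANCOVA | Log, interaction | Log, ANCOVA |
|---|---|---|---|---|
| 0.3 | 81% | 89% | 88% | 92% |
| 0.5 | 37% | 44% | 46% | 51% |
| 0.8 | 13% | 16% | 20% | 22% |

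Hand check of the log columns at log-SD 0.3, where the effect is ln 0.85 = −0.163:
- Interaction: SE = 0.3 × √(2 × 0.3) × √(2/40) = 0.0520. Then 0.163/0.0520 = 3.13, and power = Φ(3.13 − 1.96) = 88%.
- ANCOVA: SE = 0.3 × √(1 − 0.49) × √(2/40) = 0.0479. Then 0.163/0.0479 = 3.39, and power = Φ(3.39 − 1.96) = 92%.

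**4. Splitting the gain.** From the mm² interaction to the log ANCOVA, power rises by 11, 14 and 9 points at log-SD 0.3, 0.5 and 0.8. Taking baseline adjustment first, it supplies 8, 7 and 3 of these points. The log scale, with adjustment held fixed, adds 3, 7 and 6.

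**5. If the area is not skewed.** With normal data and an additive effect at r = 0.7, the log interaction has power 0.92 against 0.92 in mm² at coefficient of variation (CV) 0.25, and 0.78 against 0.81 at CV 0.3. With baseline adjustment in both analyses, the log scale costs about 2 to 6 points at these CVs.

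**6. Validity.** Under a lognormal null with 40 per arm, CV 0.3 to 1.0 and r 0.5 to 0.9, the type I error of the interaction test is about 0.044 to 0.054 on either scale.

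**The case against.** The strongest reply is that the transformation and the action after a normality check are usual content of a full analysis plan, which is not shown. On this view the article states a test, a model and an effect of interest, none of them wrong. This stands for Shapiro-Wilk: the article is silent on what follows. A reader might infer that the same ANOVA will be run whatever the result, or that a switch will be made after seeing the data. The text supports neither. The reply does not dispose of the rest, because the model and its effect of interest are stated, and a better choice costs almost nothing.

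A second reply is that the 15% defines within-person improvement and is not the tested estimand. Testing a mean difference and reading individual change against a threshold can coexist; the pain intensity section does the same with 2 points. This stands. A reader might infer that the mm² analysis contradicts the criterion or inflates false positives. It does neither.

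A third reply is that the benefit of logs rests on skewness the documents do not report, and that much of the apparent gain comes from baseline adjustment. Both parts are right, as steps 4 and 5 of the working show. An unconditional claim that the log scale gains power is not supported, nor is a log scale for pressure pain threshold, for which no evidence of skewness is available.

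**Conclusion.** The point holds as one of efficiency and interpretability. The planned comparison of CoP area is a valid but unadjusted difference in mm² change, while improvement is judged in per cent.

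The firmest part is baseline adjustment. At an assumed r = 0.7 it cuts the variance by 15% and, in mm² with lognormal data, lifts power by about 3 to 8 points across log-SD 0.3 to 0.8. The log scale is a conditional addition: about 3 to 7 points if the area is right-skewed, against a loss of about 2 to 6 points if it is near-normal with an additive effect. Its other merit, a result expressed as a relative change, does not depend on skewness.

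It is tempting to read 0.85 as a pass mark for the between-arm ratio. The article defines the 15% as a pre-post change, so it can only be a reference value there. Log-SD, r and the distributional shapes are all assumptions.

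**What to change.** Before unblinded data are seen, and independently of any Shapiro-Wilk result:

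- Replace the group x time interaction, for CoP area and for pressure pain threshold, by an ANCOVA of the post-intervention value on arm and baseline value. Nothing here supports changing the scale for pressure pain threshold.
- For CoP area, make log area (with log baseline) the primary scale. Report the between-arm ratio of geometric means with a 95% confidence interval, and give the baseline-adjusted mm² analysis as a sensitivity analysis.
- State that the 15% is a pre-post threshold and serves only as a reference when the between-arm ratio is interpreted.
- Drop Shapiro-Wilk, or state that it does not decide the analysis; inspect model residuals instead.

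The cost is a few sentences of analysis wording, with no change to data collection or sample size. The small downsides are that results for CoP area become ratios, so raw means in mm² should be shown alongside, and that a little power is lost if the area proves near-normal.

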**Methods:**

A two-arm, placebo-controlled clinical trial with parallel groups and examiner-blinded will be conducted with 80 participants with cLBP from an outpatient physical therapy department, randomly allocated at a 1:1 distribution. The experimental group will receive a lumbar spinal manipulation technique, and the placebo group will receive a simulated lumbar spinal manipulation. Both groups will receive one session of treatment and will be evaluated before and immediately after the intervention. The primary outcomes will be the pressure pain threshold and postural stability. Pain intensity and patient’s expectation will be assessed as a secondary outcome. The pressure pain threshold will be assessed using a pressure algometer in 6 different anatomical regions. The evaluation of postural stability will be performed in a baropodometry exam by displacing the centre of pressure. The pain intensity will be measured using the Numeric Pain Rating Scale. A Likert scale will be used for the patient’s expectation about the treatment. A two-way analysis of variance will compare the effect of the interventions between groups.

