### Randomisation, allocation, blinding, and implementation procedures

Participants will be randomly allocated at a 1:1 distribution to one of two groups: the experimental group (group 1) will receive a lumbar spinal manipulation technique, and the placebo group (group 2) will receive a simulated lumbar spinal manipulation technique. The allocation sequence will be prepared a priori using the “Research Randomizer”, an online random number generator available at https://www.randomizer.org/. Participants will be allocated to the experimental group (group 1) or placebo group (group 2) using randomly permuted blocks of 4 and 6. Allocation will be concealed through sequentially numbered consecutively (1 to 80), sealed, opaque envelopes with an index card containing a sentence that will inform the examiner of the participant’s group allocation. An independent examiner not involved in the study recruitment, assessment, or data analysis will assign interventions to ensure secret allocation. The same examiner will open the sealed envelopes after the informed consent form has been completed, and the participant carries out the initial assessment. The participants will receive a unique study enrolment number and be referred to the physiotherapist responsible for the intervention that will perform spine manipulation or simulation of spine manipulation according to the group in which the participant was allocated.

After performing the pre-intervention evaluation, the examiner (examiner 1) will leave the evaluation room to remain blind to the intervention, and a physiotherapist (examiner 2) with experience in spinal manipulative therapy will enter the room to perform the manipulation technique or the simulated technique according to the previous randomisation. Examiner 2 will also be blinded to the outcome assessment. After the intervention, examiner 1 will return to the evaluation room and repeat the same evaluation performed before the intervention.

Participants will be informed that they will receive a spinal manipulative therapy or a simulated spinal manipulative therapy and that both techniques can produce therapeutic effects. To verify the success of blinding strategies, participants will be asked after treatment what treatment they think they received, with two response options: (1) spinal manipulation treatment or (2) sham spinal manipulation treatment.

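### The planned group-by-time interaction is a valid change-score test, but adjusting for the baseline already collected would be more precise

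*Protocol article*

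**What the plan says.** The protocol article fixes the method for pressure pain threshold, postural stability and pain intensity in its Data analysis section: the comparison of groups on "postural stability, and pain intensity will be performed by two-way ANOVA". The same section names the test that counts: "For each ANOVA, the metric of interest will be bidirectional interaction (intervention group x evaluation time"). It adds a follow-up step, "The Bonferroni post hoc test will be used when a significant" F value is found, without saying which F is meant.

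The Sample size calculation section describes the model as "an alpha of 0.05 in a two-way analysis of variance (ANOVA) repeated measures". The Abstract uses the shorter form: "A two-way analysis of variance will compare the effect of the interventions between groups".

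There are exactly two measurement occasions: "Both groups will receive one session of treatment and will be evaluated before and immediately after the intervention". The procedure is the same on both, since "examiner 1 will return to the evaluation room and repeat the same evaluation performed before the intervention". The baseline is taken before allocation is revealed: "The same examiner will open the sealed envelopes after the informed consent form has been completed, and the participant carries out the initial assessment". The protocol does not use the baseline value as a covariate.

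**The concern.** In a design with two arms and two times, the interaction F is the square of the t statistic comparing mean change between arms. A change score subtracts the baseline with a fixed slope of 1. When the true regression of post on pre has a slope below 1, that subtraction adds noise and over-corrects any chance baseline difference. Estimating the slope avoids both problems, and the data needed are already being collected before allocation.

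What is at stake is precision on all three outcomes tested this way. The trial was sized at 80% power, and the article states no allowance for dropout, so the lost precision has a use.

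A smaller matter is the trigger for the post hoc step. A two-way ANOVA yields three F tests (group, time, interaction). As worded, any of them could set off the Bonferroni comparisons. A significant time effect alone says nothing about manipulation versus sham.

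**Working it through.** **Inputs from the protocol.** Two arms allocated 1:1, 40 per arm, two-sided alpha 0.05, 80% power, effect size 0.64 (read as a standardised mean difference), two time points, baseline measured before the envelope is opened.

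**Assumed inputs.** The pre-post correlation r is not in the documents, so a range is shown. Pre and post variances are taken as equal (σ²). The protocol does not say whether 0.64 is in units of the change-score SD or of the single-occasion SD, so both are worked.

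**Step 1: the stated sample size.** For a two-sample t-test with d = 0.64, the noncentrality at 40 per arm is 0.64 × √(40/2) = 2.86 on 78 df. Power is 80.7% at 40 per arm and 79.7% at 39, so 40 per arm reproduces exactly. The normal approximation gives 39.

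**Step 2: interaction equals change-score test.** In a simulated data set of 40 + 40, the interaction F and the squared change-score t were both 0.067758.

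**Step 3: relative precision.**
- Variance of the arm difference in change: (2/n) × 2σ²(1 − r).
- Variance of the baseline-adjusted arm difference: (2/n) × σ²(1 − r²).
- Ratio: (1 − r²) / [2(1 − r)] = (1 + r)/2.

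**Step 4: power at 40 per arm if 0.64 is in change-score SD units.** The planned test has 80.7% power whatever r is. The adjusted analysis has an effective d of 0.64/√((1+r)/2), noncentrality d × √20, and 77 df.

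| Assumed r | Variance ratio | Effective d | Noncentrality | Power, adjusted | n per arm for 80% |
|---|---|---|---|---|---|
| 0.5 | 0.75 | 0.739 | 3.30 | 90.4% | 30 |
| 0.7 | 0.85 | 0.694 | 3.10 | 86.6% | 34 |
| 0.8 | 0.90 | 0.675 | 3.02 | 84.6% | 36 |
| 0.9 | 0.95 | 0.657 | 2.94 | 82.6% | 38 |

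**Step 5: power at 40 per arm if 0.64 is in single-occasion SD units.** The change-score test has d = 0.64/√(2(1 − r)), and the adjusted analysis d = 0.64/√(1 − r²).

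| Assumed r | Change score | Adjusted |
|---|---|---|
| 0.3 | 66.6% | 84.2% |
| 0.5 | 80.7% | 90.4% |
| 0.7 | 95.4% | 97.7% |
| 0.8 | 99.4% | 99.7% |

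**Step 6: cost of estimating the slope.** It takes one degree of freedom and multiplies the variance by about 1 + 1/76 = 1.013. Break-even is (1+r)/2 × 1.013 = 1, or r of about 0.97. The power figures in steps 4 and 5 allow for the degree of freedom but not for this small factor.

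**Step 7: simulation, which includes the slope cost.** With 4,000 replicates per scenario and 0.64 in change-score SD units, power for change score versus adjusted analysis was 81.5% versus 90.7% (r = 0.5), 81.4% versus 87.3% (0.7) and 81.6% versus 82.9% (0.9). The empirical variance ratios were 0.74, 0.85 and 0.97. Type I error lay between 4.6% and 5.9% across both methods.

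**Step 8: chance imbalance.** With 40 per arm, the baseline difference between arms has SD σ√(2/40) = 0.22σ. Given such a difference, the change-score estimate is shifted by (1 − r) times it in the opposite direction. At r = 0.5 that is 0.11σ, about 17% of 0.64σ.

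**The case against.** The strongest reply is that nothing here is invalid. The planned test is a between-arm comparison, unbiased under randomisation, and it keeps its alpha. It also meets the protocol's 80% target if 0.64 is on the change-score scale. All of that stands: the point is about efficiency.

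The size of the gain is also open. Pressure pain threshold is the mean of three readings, repeated within one session by a method the protocol calls highly reproducible. A high r is plausible, and at r = 0.9 the gain is about 2 power points. If 0.64 is in single-occasion units and r is 0.7 or more, power is already above 95%. This stands too, and is why a range is given.

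Four stronger readings are tempting, and the documents do not support them.

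- *The interaction is always less precise.* It is not: above r of about 0.97 the cost of estimating the slope outweighs the gain.
- *The planned test ignores baseline imbalance.* It subtracts the baseline in full; the fault is over-correction when the slope is below 1.
- *Pairing will be ignored.* The Abstract and Data analysis sections omit the term repeated measures, and an unpaired two-way ANOVA would inflate the interaction variance by 1/(1 − r), or 2- to 5-fold for r from 0.5 to 0.8. But the Sample size calculation section names a repeated-measures model and the Data analysis section has evaluation time as a factor. The shorter name is best read as shorthand.
- *Efficacy will be claimed from within-arm change.* The sentence after the Bonferroni rule makes the interaction the metric of interest, and no within-arm test is named. The loose trigger needs tightening but does not show such an intention.

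**Conclusion.** The point holds as a recommended improvement, not as an error that invalidates the trial. The primary test is exactly a change-score comparison, and adjusting for the pre-allocation baseline is more precise at any r below about 0.97. With 0.64 in change-score SD units, the gain at 40 per arm runs from about 10 power points at r = 0.5 to about 2 at r = 0.9. In sample-size terms this is 30 to 38 per arm instead of 40 for the same 80% power. The direction of the result is secure. Its size rests on an assumed r, on equal pre and post variances, and on the unstated scale of the effect size. The post hoc trigger is a secondary matter of wording.

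**What to change.** - Make the primary analysis of pressure pain threshold, postural stability and pain intensity a linear model of the post-intervention value on arm and the outcome's own baseline value.
- Report the adjusted between-arm difference with its 95% confidence interval and p-value.
- Keep the group-by-time interaction as a sensitivity analysis, and call it repeated-measures wherever it is named.
- Restrict the Bonferroni step to a significant interaction and label it descriptive, or delete it. A single one-degree-of-freedom arm contrast needs no post hoc test.

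**Cost.** No new patients or measurements, and one degree of freedom per model. JASP, which the protocol already names, can fit the model. Recruitment began in November 2021 according to the Trial status section, and the section on communicating protocol amendments lists analyses among the changes to be notified. The change should therefore be notified under that section and made before unblinded data are analysed.

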### Outcome measures

The primary outcomes will be pressure pain threshold and postural instability. Secondary outcomes will include pain intensity and patient’s expectation.

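### Two primary outcomes, one of them measured at 12 points with no primary variable named, are each tested at 0.05 with no error control across outcomes or sites

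*Protocol article*

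**What the plan says.** Outcome measures in the protocol article: "The primary outcomes will be pressure pain threshold and postural instability". The Methods part of the abstract adds "The pressure pain threshold will be assessed using a pressure algometer in 6 different anatomical regions", and Evaluation of the pain threshold says "The evaluation points will be measured bilaterally three times in the following places". Six sites on two sides make 12 points, running from the lumbar spine (L1, L5) to calf, tibialis anterior, deltoid and lateral epicondyle. The only data reduction stated is "For data analysis, the average of the three values obtained in each evaluation measure by pressure algometer in pre- and post-intervention will be used", which concerns the three repeats.

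Postural stability is a single variable: "The stability variable investigated using the baropodometer will be the area of the CoP ellipse".

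Data analysis compares the groups by two-way ANOVA. It says "For each ANOVA, the metric of interest will be bidirectional interaction (intervention group x evaluation time"), and then "All statistical tests will be two-tailed with the pre-established significance level at" p < 0.05. The one adjustment named is a Bonferroni post hoc test, used once an F value is significant.

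Sample size calculation gives 40 per group at 80% power and alpha 0.05 "to detect a minimum difference of 15% (effect size of 0.64) in the low-pressure pain threshold", without naming a site or side.

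The article does not state a primary PPT site, side or composite, the number of PPT ANOVAs, or whether one or both primary outcomes must be significant. The hypothesis at the end of the Introduction mentions both outcomes but sets no decision rule.

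**The concern.** With two primary outcomes and a per-test level of 0.05, the error rate of the primary conclusion depends on how many tests feed it and what counts as success. The protocol fixes neither. PPT could be one test, six or 12, and the choice could be made after the data are seen.

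The Bonferroni step does not close this gap. With two groups and two time points the group-by-time interaction has one degree of freedom and is itself the treatment test. Post hoc comparisons after it only describe a result already declared significant. They do nothing about the next site or the other outcome.

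At stake is whether a primary claim for manipulation over sham could rest on one favourable site. Also, the 80% power belongs to a single unnamed PPT test and not to the primary analysis as a whole.

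**Working it through.** **Inputs from the protocol.** Two primary outcomes; six PPT sites on two sides; one A-CoP variable; two-sided 0.05 per test; effect size 0.64; 40 per group; 1:1 allocation.

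**Step 1: reproduce the sample size.** Normal approximation: n per group = 2 × (1.96 + 0.84)² / 0.64² = 38.3, so 39. Exact noncentral t with 40 per group: df = 78, noncentrality = 0.64 × √(40/2) = 2.86, power 80.7% (39 per group gives 79.7%). The stated 40 per group is reproduced. This is the one-degree-of-freedom interaction test if 0.64 is the between-group difference in change divided by the SD of change. Entering 0.64, or half of it (0.32), as Cohen's f in repeated-measures ANOVA formulas with correlation 0 or 0.5 gives totals of 8 to 60, not 80. So 0.64 was evidently used as a standardised mean difference for one test at 0.05.

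**Step 2: independent tests.** The chance of at least one false positive among k tests, with no true effect anywhere, is 1 − 0.95^k:
- k = 2 (PPT reduced to one value, plus A-CoP): 1 − 0.9025 = 9.75%
- k = 7 (six sites, sides pooled, plus A-CoP): 30.2%
- k = 13 (12 points plus A-CoP): 48.7%

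**Step 3: correlated PPT tests.** Site results within a person are correlated, and the protocol gives no correlation, so a range is assumed. Each PPT statistic was simulated as Z_j = √ρ·S + √(1−ρ)·E_j, with A-CoP independent, significance at |Z| > 1.96 and 400,000 draws. Here ρ is the correlation between the test statistics, that is, between the pre-to-post changes at different points.

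| Assumed ρ | 6 sites + A-CoP | 12 points + A-CoP | 6 sites alone | 12 points alone |
|---|---|---|---|---|
| 0 | 30.2% | 48.9% | 26.5% | 46.1% |
| 0.5 | 24.6% | 35.2% | 20.7% | 31.8% |
| 0.7 | 20.7% | 27.2% | 16.5% | 23.3% |
| 0.8 | 18.2% | 22.6% | 13.8% | 18.6% |
| 0.9 | 15.3% | 17.8% | 10.8% | 13.5% |

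The simulated 48.9% agrees with the exact 48.7%. The last two columns show what remains if A-CoP is set aside and any significant site counts as a PPT effect.

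**Step 4: power under control.** With d = 0.64 and 40 per group, noncentral t power is 80.7% at alpha 0.05, 71.7% at 0.025, 54.2% at 0.05/7 and 45.8% at 0.05/13. Adjusting across every site is therefore expensive; naming one PPT variable first is not.

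**The case against.** The strongest reply is that the article never says each site gets its own ANOVA. It speaks of PPT as one outcome throughout, and a journal article condenses a fuller protocol or analysis plan in which the site reduction and multiplicity procedure may be set out. On that reading there are two tests, and the figure is about 10%. This stands as far as it goes: the number of PPT tests is unspecified, not known to be six or 12. It does not remove the point. The article itself sets 0.05 for all tests, names its only adjustment, and bases the sample size on a PPT variable that it does not identify.

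A second reply is that the hypothesis joins the two outcomes, so both may be required. If so, there is no inflation between them. No such rule is written, however, and the choice among PPT sites would remain: under no PPT effect, the sites alone give 11-26% (six) or 13-46% (12).

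A reader might infer that the false positive rate simply is 20-50%. The documents do not support that. It requires separate tests per site or point and correlations of about 0.7 or less, and the upper end requires zero correlation among 12 points in one person, including left and right of the same muscle. A reader might also say that the plan has no error control at all. A Bonferroni step is named; it acts in the wrong place for this purpose.

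**Conclusion.** The point holds: the primary PPT variable is undefined, and nothing stated controls error across the two outcomes or the PPT sites. The size is conditional. Counting any one significant primary test as success, and taking A-CoP as independent of PPT, the false positive chance is about 10% with one PPT test. If sites are tested separately, it is about 15-30% with six and 18-49% with 12, for assumed correlations of 0.9 to 0. Even the most favourable any-one-suffices reading with independent outcomes is about double the nominal 5%. That the trial would declare success on any one of 7 to 13 tests is something a reader might infer; no success rule of any kind is stated.

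The 80% power applies to one unspecified PPT test at 0.05. No effect size is given for A-CoP, so its power is unknown.

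**What to change.** Before analysis:

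1. In Evaluation of the pain threshold, name a single primary PPT variable and make the remaining sites secondary. The bilateral mean of the L1 and L5 points is one option, since the lumbar spine is what is treated; another single prespecified site or composite would also serve.
2. In Data analysis, test that variable and A-CoP with Holm or Hochberg at an overall two-sided 0.05, or state that both must be significant for the trial to be positive. Say that the Bonferroni post hoc test is descriptive and lies outside this control.
3. In Sample size calculation, say which PPT variable the 0.64 refers to and that the 80% power is for that one test at alpha 0.05. If 0.64 is the standardised difference in change for the named variable, power is about 81% at alpha 0.05 and about 72% at 0.025. State that no effect size was set for A-CoP.

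The 72% should not be copied in unless that condition is met. If 0.64 describes a single point, a mean of four points with the same effect and between-point correlation r has d = 0.64 / √((1 + 3r)/4). That is 0.73 at r = 0.7 and 0.81 at r = 0.5, with power at alpha 0.025 of about 83% and 91%.

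The cost is wording and a somewhat less favourable stated power, with no extra patients or measurements. The article's section on communicating protocol amendments already covers changes to outcomes and analyses.
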